### Procedure

#### Data collection and individual counseling.

Study subjects will be monitored for motor awareness (Rate of Perceived Exertion [RPE] of 14 at lactate threshold) through individual counseling, and all voluntarily consented data will be collected, including responses to the app-embedded questionnaire, interview data, and blood samples. All voluntary consenters will be registered in the provided app.

#### Pre-preparation for the exercise program.

Before starting the exercise program, subjects will be informed and prepared through a professional consultation with an exercise physiologist about exercise awareness.

#### Exercise intensity.

The exercise intensity will be set to reach the lactate threshold based on an RPE of 14.

#### Counseling schedule.

Individual counseling sessions will be held at the beginning of the study, after 1½ months, and at the end of 3 months.

### Assessment

Primary outcome measures:

**Short physical performance battery (SPPB**): A physical activity measurement tool that provides a simple and reliable assessment of a subject’s physical function

Grip strength assessment:

Measures handgrip strength to assess hand and arm muscle strength

Activity-specific balance confidence (ABC):

Uses the ABC scale to assess a subject’s confidence in balance.

Muscle strength evaluation:

Assesses muscle strength levels by measuring maximum strength and peak power.

Appendicular skeletal muscle mass (ASM):

Measures the amount of skeletal muscle mass in a subject through body composition analysis using Dual Energy X-ray Absorptiometry (DXA).

One repetition maximum strength (1RM) and stair climbing power test:

Measures 1-rep max strength (1RM) and stair climbing power to assess a subject’s strength and power capacity.

### Privacy protections

This study will utilize data collected from the time IRB approval is received until the end of the study. All personal information collected from study participants will be processed into numerical codes and converted into de-identified secondary data, which will be securely stored and analyzed on the principal investigator’s computer and external hard drive.

The collected personal information (name, gender, date of birth, affiliation, contact information, email, address, past medical history, and medication status) will be used only during the study period and will be kept for 3 years after the study ends, then destroyed in accordance with Article 15 (2) of the Enforcement Rules of the Act on Bioethics and Safety.

The results of the study will only be reported in the form of aggregated data, not individualized information, and if a participant drops out of the study, the data will be immediately deleted from the principal investigator’s external hard drive and the related documents will be destroyed through a shredder. After the end of the study, all study-related data (including data on suspension and withdrawal) will be stored for 3 years in a secure cabinet in the archive located in Cheonma Gymnasium Room 103, after which the information will be permanently deleted. If personal information is leaked, we will compensate for damages in accordance with relevant legal procedures.

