### Subject selection criteria and methods

Subjects will be selected based on the following criteria:

300 registered participants of the Health and Exercise Center who participate in exercise at least once a week and voluntarily agree to participate in the study.100 patients registered at Yeungnam University Medical Center.100 members of the general public who do not participate in exercise.

The total number of subjects is set at 500 for the 3-month study period, and the study will be conducted on subjects who agree to participate after being provided information about the study. Written informed consent will be obtained after the exercise specialist confirms that the subject meets the requirements for participation.

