### Rationale for subject selection

In this study, we aim to have a sufficient sample size to compensate for the limitation of our previous study [20], which did not yield significant results due to a small sample size (N = 63) while exploring candidate genes through genome-wide association studies (GWAS). To this end, we plan to recruit at least 500 subjects by setting the power (1-β) at 0.8, the effect size at 0.5, and the significance level (α) at 0.05 using the G-power program.

Additionally, after accounting for non-respondents and voluntary/dropouts, the final study population is expected to be around 400. This sample size will increase the statistical significance of the study and contribute to strengthening the reliability of the findings.

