**Fig 3 pone.0327947.g003:**
[figure not shown]
Diagram algorithme.

To evaluate the effectiveness of the exercise intervention, all participants will be measured three times. Data will be de-identified with a numeric code per subject and managed so that only the principal investigator will have access to all participants’ identifying information.

2Exercise interventions

The study will be a 3-month, parallel-group, randomized controlled trial consisting of cancer patients (100) and non-cancer patients (300). The cancer patient group will consist of patients undergoing treatment or post-operative rehabilitation, while the non-cancer patient group will include subjects at more than twice the risk of developing the disease, members of exercise centers, and those who only use ICT apps.

The cancer patient group will be provided with a tailored exercise program to improve cardiorespiratory fitness and muscle strength, which will aim to improve physical function and quality of life.

The **EXESALUS program** is designed so that participants start the exercise intervention within 10 days of enrollment, once their health risk results are confirmed through genetic testing.

If a subject is unable to start the exercise intervention, it will be recorded as a ‘protocol intervention withdrawal.’

Psychological counseling by a clinical psychologist will be provided twice, once before starting the exercise intervention and again at 2-months, to ensure study participation and ongoing motivation.

3-1EXESALUS Exercise Program

The EXESALUS exercise program (http://exesalus.com) is an ICT-based personalized exercise intervention program for health promotion and disease prevention (Fig 4). The program provides a variety of exercises targeting the upper body, lower body, abdomen, and whole body (adjusted by intensity) and provides five workouts per week for 3 months, ranging from low to high intensity, using exercises that are appropriate for the target audience. The goal is to build muscle strength and improve psychological well-being.

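### The rule to delete data when a participant drops out conflicts with the 3-year retention rule and, if applied as written, leaves a completers-only analysis

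*Protocol article*

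**What the plan says.** All places are in the protocol article.

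- **Privacy protections, deletion:** "if a participant drops out of the study, the data will be immediately deleted". The only store named for this is the external drive. For papers, the rule is that "the related documents will be destroyed through a shredder". The trigger is dropping out, with no further qualification.
- **Privacy protections, retention:** the next sentence states that after the end of the study "all study-related data (including data on suspension and withdrawal) will be stored for 3 years".
- **Privacy protections, storage:** coded data are "securely stored and analyzed on the principal investigator’s computer and external hard drive". The deletion rule names only the second of these stores.
- **Preservation and disposal of human remains:** specimens are destroyed on withdrawal of consent or at the end of the study. This trigger is narrower than the one for data.
- **Exercise interventions (item 2):** "If a subject is unable to start the exercise intervention, it will be recorded as a" withdrawal from the protocol intervention. Everyone is to be measured three times.
- **Treatment of missing data:** the cause of missingness is to be identified. A sensitivity analysis follows if data are missing at random (MAR); listwise or case deletion is for data missing completely at random (MCAR).
- **Subject selection criteria and methods:** "The total number of subjects is set at 500 for the 3-month study period".
- **Rationale for subject selection:** after non-response and dropout, "the final study population is expected to be around 400".

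**The concern.** Two adjoining sentences give staff instructions that seem incompatible for the same records. If the deletion sentence is the one followed, the consequence is statistical as well as administrative. With three measurements over 3 months, a dropout will often leave a baseline value and perhaps a 6-week value. A MAR analysis works from those values. Erasing them imposes case deletion on every dropout whatever the mechanism, although the missing-data section reserves case deletion for MCAR. It also removes the evidence needed to judge the mechanism, since dropouts could not be compared with completers even at baseline.

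Dropout could well differ between the groups. One is offered five workouts a week, while the other carries on with daily life and monitors itself with a wearable device. A difference of this kind can bias a completers-only comparison, and once the records are gone nobody could tell whether it had. An analysis plan that is not shown could not repair this, because it cannot recover destroyed data.

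**Working it through.** **1. The plan's own figure.** 500 enrolled, about 400 remaining: 500 − 400 = 100 lost, and 100/500 = 20%. In reverse, 400/(1 − 0.20) = 500. The step is consistent. The 100 include non-respondents, so fewer than 100 may be dropouts with data to delete.

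**2. Power is not the harm.** For the planning effect of 0.5 SD at two-sided 0.05, 400 people give power above 0.99 if split 200 v 200, and 0.98 if split 320 v 80. What matters is bias.

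**3. Bias formula.** Let g be the gap, in SD, by which completers do better than dropouts, assumed the same in both groups. Let p_E and p_C be the dropout rates in the exercise and control groups. A completers' mean exceeds the mean of everyone in the group by p × g. The completers-only difference is therefore off by

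bias = g × (p_E − p_C).

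The document gives neither g nor dropout rates by group, so all values below are assumptions. The group sizes are also assumed: 400:100 in the second and third rows, 250:250 in the fourth. Each unequal row has 100 losses in total.

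| Assumed dropout, exercise v control | Check on losses | g = 0.25 | g = 0.5 | g = 1.0 |
|---|---|---|---|---|
| 20% v 20% | 20% of 500 = 100 | 0 | 0 | 0 |
| 24% v 4% | 0.24×400 + 0.04×100 = 100 | 0.05 | 0.10 | 0.20 |
| 25% v 0% | 0.25×400 = 100 | 0.06 | 0.125 | 0.25 |
| 30% v 10% | 0.30×250 + 0.10×250 = 100 | 0.05 | 0.10 | 0.20 |

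(Bias in SD.)

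**4. Effect on type I error, 24% v 4% row.**
- Remaining: 400 − 96 = 304 and 100 − 4 = 96.
- SE = √(1/304 + 1/96) = 0.117 SD.
- g = 0.25: shift 0.05/0.117 = 0.43 SE; P(|Z| > 1.96) is about 7%.
- g = 0.5: shift 0.10/0.117 = 0.85 SE; 13.7%.
- g = 1.0: shift 0.20/0.117 = 1.71 SE; 40.1%.

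The nominal rate is 5%.

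**5. The missing-data steps against the deletion rule.**

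| Planned step | People who stay but miss a visit or item | Dropouts, if deletion is carried out |
|---|---|---|
| Identify the cause | Possible | Not from the deleted records |
| MAR sensitivity analysis | Possible | Unworkable: no observed values left |
| Case deletion only under MCAR | Possible | Imposed whatever the mechanism |

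**The case against.** Several stronger readings are tempting, and the document does not support them.

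- **That deletion is total and so forces a completers-only analysis.** The clause names the external drive only. The computer copy is not addressed, and no deletion rule is given for data entered in the study app or for results from the outside laboratory that handles the buccal swabs. Shredding the papers suggests that full removal is meant, but the text does not settle it. Moreover, if the two sentences conflict, the fate of dropouts' data is undetermined. The consequence is therefore conditional on the rule being applied as written.
- **That the whole missing-data plan becomes impossible.** It still serves missed visits and items among those who stay. It fails only for dropouts.
- **That non-starters' data are deleted.** The exercise section says only that they are recorded under a withdrawal label. That label might even be meant to separate leaving the intervention from leaving the study.
- **That all 100 expected losses are dropouts whose data would be destroyed.** The figure includes non-respondents.
- **That deletion alone defeats analysis by allocation.** The Control group section defines that group by genetic risk, and the Statistics section compares active with inactive people. Such an analysis is already in doubt on those grounds.

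The retention sentence also has a milder reading: it may mean records about withdrawals, much as disposal records are kept after specimens are destroyed. The contradiction is therefore apparent, not certain. Finally, unequal dropout is assumed in the calculation, and with equal rates and equal gaps the bias vanishes.

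All of this limits the claim. It does not remove it: the stated trigger is any dropout, and following it destroys data that the missing-data section needs.

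**Conclusion.** The point holds in a conditional form. The deletion trigger is wider than withdrawal of consent, appears to contradict the next sentence, and, if carried out as worded, confines the analysis to completers and makes the MAR step unworkable for dropouts. The bias in SD runs from zero (equal dropout and equal gaps) through 0.10 (24% v 4%, 0.5 SD gap, type I error about 14%) to 0.20 (same dropout, 1.0 SD gap, about 40%). It would reach 0.25, half the planning effect, if all 100 losses fell among 400 exercisers with a 1.0 SD gap. These sizes rest on assumed group sizes, dropout rates and gaps. They show what could go undetected and are not a forecast. Because the study is described as ongoing and deletion cannot be undone, the wording should be settled promptly.

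**What to change.** Reword Privacy protections as follows:

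1. Stopping the programme, never starting it, or missing visits does not trigger deletion.
2. Coded data collected up to that point are kept and analysed in the participant's assigned group.
3. These participants continue to be invited to the planned 6-week and 3-month measurements.
4. Data are erased only on an explicit request for erasure, in every place where they are held, and the number of such requests is reported by group.
5. The deletion and retention sentences are made to agree, and both are reconciled with the sections on disposal of human remains, exercise interventions (the withdrawal label) and treatment of missing data.

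The cost is an ethics board amendment with matching consent wording and some extra follow-up invitations. The downside is that dropouts' coded data are held for longer.

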### Treatment of missing data

The best way to deal with missing data is to plan your research well and collect data carefully to avoid problems. Identify the cause of the omission to minimize the amount of missing data in clinical studies. In this study, if the missing data followed Missing-at Random (MAR), a sensitivity analysis was performed to minimize bias and draw valid conclusions. If the data was MCAR (Missing Completely at Random), the data was deleted by Listwise or case deletion and the data were evaluated [22].

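### The missing-data rule turns on a mechanism the data cannot establish, and it names no primary estimator when data are missing at random

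*Protocol article*

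**What the plan says.** Treatment of missing data, in the protocol article, gives two branches. One is "If the data was MCAR (Missing Completely at Random), the data was deleted by Listwise or case deletion and the data were evaluated". The other is "if the missing data followed Missing-at Random (MAR), a sensitivity analysis was performed to minimize bias and draw valid conclusions". It gives no procedure for deciding which branch applies, and MNAR does not appear.

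Four other places bear on this:

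- **Statistics** centres the analysis on the t-test and ANOVA, comparing active with not active participants.
- **Randomization and exercise intervention adjustment** says "all participants will be measured three times". Study design dates the three biospecimen collections at the start, 1½ months and 3 months.
- **Rationale for subject selection** says "we plan to recruit at least 500 subjects" and that "after accounting for non-respondents and voluntary/dropouts, the final study population is expected to be around 400".
- **Privacy protections** says that a dropout's data are deleted at once from the investigator's drive and the related documents shredded. It then says that study data, including those on suspension and withdrawal, are kept for 3 years.

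**The concern.** The rule cannot be applied as written. Observed data may contradict MCAR but cannot establish it, and they carry no information that separates MAR from MNAR. The choice of method would therefore be made after the data are seen, on grounds the data cannot supply.

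The MAR branch also gives a sensitivity analysis the wrong job. Such an analysis tests a primary estimate and does not supply one. With no estimator named, the only analyses left are the t-test and ANOVA, which on change scores use only people with a final value.

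Selective loss is plausible here. One group is offered five workouts a week, up to high intensity, while controls keep their usual routine. If participants doing poorly at 6 weeks leave the exercise group, those who stay look better than the whole group would have. The interim measurement could correct this, but the plan gives it no role, and the deletion sentence under Privacy protections could remove it.

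**Working it through.** **Expected loss.** (500 − 400)/500 = 20%. This covers non-respondents as well as dropouts, so the share lost after enrolment lies somewhere between near 0 and 20%.

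**Is the threat power or bias?** The stated inputs include "setting the power (1-β) at 0.8" and "the effect size at 0.5". Read the effect size as a standardised mean difference at two-sided 5%, with 400 analysed.
- Equal groups: SE = √(1/200 + 1/200) = 0.100; power = Φ(0.5/0.100 − 1.96) = Φ(3.04) = 0.999.
- 4:1 groups: SE = √(1/320 + 1/80) = 0.125; power = Φ(4.00 − 1.96) = Φ(2.04) = 0.979.

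Power survives the loss, so the issue is bias. (The 500 itself does not follow from its inputs: two-sided 1:1 needs 63 per group, 126 in all. That is a separate matter and nothing here depends on it.)

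**Assumptions for the bias.** The documents give none of these: 400 exercise v 100 control; no true effect; outcomes of SD 1 at baseline, 6 weeks and 3 months with common correlation r; outcomes measured on the biospecimen dates; exercise-group dropout after 6 weeks, logistic in the standardised 6-week change; control dropout at random. Losses of 23% and 8% give 92 + 8 = 100 people, the full 20%.

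**Formula.** Let D1 and D2 be the changes from baseline at 6 weeks and 3 months. Var(D1) = 2(1 − r) and Cov(D1, D2) = 1 − r, so D2 regresses on D1 with slope 0.5. Then

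bias = 0.5 × √(2(1 − r)) × m,

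where m is the mean standardised 6-week change among exercise-group completers. For 23% loss and logistic slope 1 per SD, numerical integration gives m ≈ 0.20.
- r = 0.7: 0.5 × 0.775 × 0.20 ≈ 0.08 SD.
- r = 0.5: 0.5 × 1.0 × 0.20 = 0.10 SD.

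**Type I error, r = 0.7.** Completers number 400 × 0.77 = 308 and 100 × 0.92 = 92. SE = 0.775 × √(1/308 + 1/92) = 0.092. The test statistic shifts by about 0.076/0.092 = 0.83, so rejection ≈ P(Z > 1.13) + P(Z < −2.79) ≈ 13%.

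**Simulated completer t-test on change scores (at least 2000 trials per setting):**

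| Loss, exercise / control | Slope | r | Bias (SD) | Type I error |
|---|---|---|---|---|
| 23% / 8% | 0.5 | 0.7 | +0.04 | 7–8% |
| 23% / 8% | 1.0 | 0.7 | +0.08 | 12–14% |
| 23% / 8% | 1.5 | 0.7 | +0.10 | about 20% |
| 23% / 8% | 2.0 | 0.7 | +0.12 | about 23% |
| 23% / 8% | 0.5 | 0.5 | +0.05 | 8% |
| 23% / 8% | 1.0 | 0.5 | +0.10 | 13% |
| 23% / 8% | 1.5 | 0.5 | +0.13 | about 20% |
| 11.5% / 4% | 1.0 | 0.7 | +0.04 | 7% |
| 20% in both, same mechanism | 1.0 | 0.7 | 0.00 | about 5% |

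In the 23%/8% settings, an estimator that uses the baseline and 6-week values had bias within 0.005 SD.

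**A different set-up** (true effect 0.50 SD, 250 per group, correlation 0.7 between the 6-week and 3-month changes):
- MCAR, 20% loss: completers give 0.50.
- MAR, 17% loss: completers give 0.68, an estimator valid under MAR gives 0.49.
- MNAR, 13% loss: 0.69 and 0.61.

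The last line shows why a MAR-based primary analysis still needs an MNAR check.

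**The case against.** The strongest reply has four parts.

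1. **Deletion is confined to the case where it is valid.** The plan uses listwise deletion only under MCAR, where it is unbiased and costs only precision the trial can spare. This stands. A reader might infer that the plan leaves no valid primary estimate at all; the documents do not support that. The gap is the MAR and MNAR cases and the unverifiable choice between branches.
2. **An article condenses the full protocol.** The name of the sensitivity method and its MNAR content could sit in a document not shown. This stands for the omissions taken alone. It does not rescue the decision rule, which the article states outright. That the t-test on available cases would be the main result under MAR is an inference from reading Treatment of missing data with Statistics; the text does not say it.
3. **The size depends on the scenario.** This stands. Group sizes, slope, correlation and one-sided dropout are all assumed, and symmetric loss gives no bias. A reader might take the 20% as dropout after enrolment, but that figure includes non-respondents.
4. **The 6-week value is not discarded by listwise deletion in the scenario described.** Dropout driven by 6-week response is MAR, which the plan does not send to listwise deletion. This stands too: the explicit loss of dropouts' earlier data comes from Privacy protections, and the retention sentence there pulls the other way.

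**Conclusion.** The point holds in this limited form. The method is chosen by a classification that observed data cannot settle, and under MAR the plan names no primary estimator, so an available-case t-test or ANOVA would stand by default.

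The consequence is bias, not lost power. Under the stated assumptions it runs from 0 to about 0.13 SD, with type I error of about 5% to 23%. That range describes the scenarios run and is not a ceiling. By the formula, slope 2 at correlation 0.5 would give about 0.12/0.775 = 0.15 SD, and the different set-up gave 0.68 − 0.50 = 0.18 SD. If post-enrolment loss is small or alike in both groups, the effect is small or nil.

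Whether the compared groups are randomised at all is a separate question. The control group is described by genetic risk and the analysis contrasts active with not active participants. Better handling of missing data does not cure that.

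**What to change.** Replace the paragraph under Treatment of missing data.

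- **Delete** the MCAR/MAR decision rule and listwise deletion.
- **Primary analysis:** a mixed model for repeated measures with baseline, group, visit, group-by-visit and cancer status, or multiple imputation using baseline and 6-week values, on all allocated participants. With baseline as a covariate, someone with no later value contributes nothing to the mixed model, so report how many there are by group.
- **Sensitivity analysis:** delta-adjusted imputation under MNAR that makes missing exercise-group outcomes progressively worse.
- **Privacy protections:** reconcile the sentence deleting dropouts' data with the one storing withdrawal data for 3 years, so that data collected before dropout are kept where consent and privacy law allow. Without this the primary analysis loses the values it relies on.

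The cost is analysis wording, some programming and possibly an ethics or consent amendment for the privacy text. No new measurement is needed if outcomes are taken at the three planned occasions. The article puts the end of data collection at February 2027, so the change can be made before analysis.
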